#### Phase 4: Intervention

The intervention is based on the model developed by Milgrom at the Australian Parent-Infant Research Institute (PIRI) at Heidelberg Repatriation Hospital (Milgrom et al., 1999, 2011, 2015a,b; Milgrom and Gemmil, 2015) to reduce maternal prenatal and postnatal depression, anxiety and parenting difficulties. Moreover, this model provides for the simultaneous assessment of the neurobiological, psychological and social factors that contribute to developing psychological vulnerability in the perinatal period.

Milgrom developed a psychosocial and psychological treatment by adapting Cognitive-Behavioral Therapy (CBT) interventions for women suffering from depression both in pregnancy and postpartum (Milgrom et al., 1999; Milgrom and Gemmil, 2015). The effectiveness of this treatment has been assessed in both short- and long-term application, and its validity has been demonstrated and compared to pharmacological therapy using antidepressants. It has been deemed more effective than drugs in maintaining long-term results (Milgrom et al., 2015a).

The intervention consists of group-based CBT and focuses on the women’s life events and mood and on practical issues. The intervention takes place primarily in groups because the group setting allows participants to meet, compare and share their experiences, offering mutual support. However, in the event of impossibility of organizing a group of at least three participants within a few weeks of the psychodiagnostic evaluation, or where a participant is unable to take part regularly in weekly group sessions due to health or organizational reasons, each healthcare center offer the option of individual treatment. This solution allows a more flexible approach than group treatment, since the program can be adapted to the specific situation of the woman in question. In both cases, information and activity material are distributed between sessions.

This clinic-based group intervention is led and facilitated by a licensed psychotherapist and consists of ten weekly sessions of 90 min exclusively dedicated to the pregnant women/new mothers, three sessions involving the partners/fathers, and another three sessions dedicated to mother–child interaction. [In our study, before this last module, the QUITs (Axia and Weisner, 2002) is administered to assess infant temperament traits]. The content of the individual counseling is the same as that of group-based counseling and consists of ten sessions of 60 min. At the end of each session, participants receive information and activity materials to be used in the next session. Between sessions, participants are encouraged to put what they have learnt/experienced during the treatment into practice in everyday life. The session program is shown in Table 2.

**TABLE 2 T2:** Treatment Program.

**Step 1: Behavioral interventions**	

Session 1	**Understanding and dealing with depression.** *The sessions involve the individual or group development of the themes of the treatment program. The first session begins with participant and the therapist introducing themselves, sharing experiences to encourage a sense of belonging within the group. This psychoeducational session invites women describe their expectations of motherhood and the therapist provides information on prenatal and postnatal depression*.
Session 2	**Pleasurable activities: where do I find the time?** *The therapist encourages the women to think about their daily routine and to talk about their difficulties, thoughts, emotions and joys. Possible pleasurable activities (to enjoy alone, with their child and with their partner) are suggested for reducing the stress and fatigue of everyday commitments*.
Session 3	**Quick relaxation strategies.** *The therapist proposes some relaxation techniques (for example, Jacobson’s progressive muscle relaxation). Together with participants, the therapist examines possible simple “stress-eliminating” techniques*.
Session 4	**Assertiveness and self-esteem: telling others what I think and how I feel.** *The therapist proposes role-playing and communication techniques intended to encourage the women to express their needs in an assertive manner*.

**Step 2: Cognitive interventions**	

Session 5	**Unrealistic expectations on childcare: how the past can influence the present.** *This session reflects on the image of motherhood and the mother. Childcare methods learned from the family of the mother-to-be are compared with those adopted in the partner’s family*.
Session 6	**My inner voice: the missing link.** *The therapist helps participants to understand the impact that thoughts, emotions and behaviors can have on mothers’ everyday life and proposes new ways to deal with negative thoughts, cognitive distortions and/or reasoning errors, by replacing them with more functional thoughts for their well-being*.
Session 7	**Developing a more effective way of thinking.** *In this and in subsequent sessions, the therapist helps participants to focus on techniques to encourage positive thoughts*.
Session 8	**Query/challenge your inner critic.** *Questioning irrational beliefs and negative/critical thoughts*.

**Step 3: Prevention of relapse**	

Session 9	**Putting it all together: “moving forward”.** *Mothers are encouraged to build and use new social networks so that they can refer to them for social support when treatment is concluded*.
Session 10	**Consolidating what I have learned.** *Session to reinforce treatment education and experiences. Mothers can bring their babies*.

**Additional clinical forms with fathers**	

Session 1	**Involving fathers: fathers and post-natal depression.** *In subsequent sessions, fathers are also involved. The therapist provides fathers with information on perinatal depression. This particular session encourages couples to express their feelings about being parents and how they have felt in the past few weeks*.
Session 2	**Couple relationship.** *This session addresses the changes that have occurred in the couple’s relationship since the baby’s birth. Couples are encouraged to communicate and spend quality time together*.
Session 3	**Do it on your own.** *Summarizing the treatment experience and looking at how each couple is dealing with issues related to planning family life with the child*.

**Additional clinical forms with the presence of children: baby H.U.G.S**	

Session 1	**Let’s play! Games and physical contact.** *The therapist introduces neonatal massage technique and talks about the feelings generated by of physical contact. Parents are presented with games for different ages and emphasis is given to the pleasure of proper mother–child interaction and the importance of non-verbal communication*.
Session 2	**Let’s learn something about our child. Observing and understanding his/her signals.** *Activities involving non-verbal interactive behavior are recommended, including stress responses. Parents are encouraged to observe and interpret the child’s non-verbal communication in a playful and fun context. The therapist introduces stimulation activities to identify differences in temperament*.
Session 3	**Let’s analyze our feelings. Parental responses to the signals of their newborn.** *Couples are encouraged to observe the differences between their needs and those of their newborn baby*.

In Italy, following the publication of the Italian language manual (Milgrom, 2003), the actual feasibility and effectiveness of Milgrom’s psychological interventions for the prevention and treatment of postpartum depression has been demonstrated by ISS research (Mirabella et al., 2016).

#### Phase 5: Follow-up

Changes in the patients’ clinical conditions are re-evaluated at three points of follow-up (end of intervention, 6th month and 12th month) using EPDS, PHQ-9, STAI, WHOQOL-BREF, QUITs, MINI-Plus and a clinical interview.

Mothers who are still depressed after the intervention phase are sent to a clinical psychological or psychiatric service.

### Study Outcomes

The data on maternal psychosocial and clinical conditions will be gathered. The primary outcomes are maternal depressive and anxiety symptoms severity. Secondary outcomes are maternal perceived quality of life and infants’ temperament (only for the infants whose mothers participated in the intervention).

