### Main Objectives

(1)In light of the above, the first objective of this study is to evaluate the prevalence of both maternal antepartum and postpartum depression and anxiety in a large sample of women attending healthcare centers in Italy.(2)The second objective, parallel to the first, is to investigate the psychosocial risks and protective factors associated with maternal antepartum and postpartum depression and anxiety.(3)The third objective, building on the first, is to evaluate the psychometric properties of both the Edinburgh Postnatal Depression Scale (Cox et al., 1987) and the Patient Health Questionnaire-9 (Kroenke et al., 2001) in detecting perinatal depression.(4)The fourth objective is to evaluate the effectiveness of a manualized psychological intervention (Milgrom et al., 1999) for both antenatal and postnatal depression in a large sample of mothers in Italy.(5)The final objective is to evaluate the influence of maternal depression and anxiety on the development of baby temperament during a period of a minimum of 12 months up to a maximum of 18 months from birth.

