#### Phase 3: Psychodiagnostic Evaluation

All mothers undergo an interview with a clinical psychologist. Within the following week, in the case of clinician-generated diagnosis of perinatal depression and/or anxiety (according to the DSM-5 criteria), these mothers are further assessed using the Mini-International Neuropsychiatric Interview (MINI) Plus (Lecrubier et al., 1997; Sheehan et al., 1998) to confirm the diagnosis, the World Health Organization Quality of Life (WHOQOL) BREF (The Whoqol Group, 1998) to assess the quality of life and the Italian Questionnaires of Temperament (QUITs) (Axia, 2002) to assess the babies’ traits in temperament.

All mothers receive verbal feedback about the results of the psychodiagnostic evaluation. Depressed and/or anxious mothers are invited to participate in the intervention phase of the study. Whereas mothers with postpartum psychotic disorders, non-suicidal self-harm tendencies or suicidal ideation are sent to a psychiatric service and excluded from the study.

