#### Italian Questionnaires of Temperament

The QUIT (Axia, 2002) is a set of questionnaires that are used to measure temperament in infants from the first month up to 11 years of age. This study uses the QUIT 1–12 and 12–36 month Scales. It is a caregiver-report questionnaire validated with reference to Italian culture, containing 55 items investigating six dimensions: attention, inhibition to novelty, motor activities, positive emotionality, negative emotionality and social orientation. The first three dimensions relate to adaptation in general, while the second three relate to specific adaptation to the social world. The answer to each item is on a six-point Likert scale with which mothers indicate their baby’s positive or negative attitude toward the environment, with higher scores indicating greater intensity of a characteristic. Four infant temperamental profiles can be obtained on the basis of the orthogonal dimensions of positive and negative emotionality: emotional temperament, calm temperament, normal temperament, difficult temperament. The QUIT has acceptable internal consistency with Cronbach’s alpha ranging from 0.59 to 0.71 (Axia, 2002), and the Pearson’s correlation coefficient among reports by mothers and fathers ranges from 0.32 to 0.62 (Axia and Weisner, 2002).

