### Data Analysis Plan

The prevalence of antenatal and postpartum depression and the risk of anxiety will be calculated and compared. Since previous studies have ascertained a higher risk of developing depression in the postpartum period, the antenatal period will be taken as a reference to calculate the odds ratio as a measure of the relative risk of depression between antenatal and postpartum periods, using chi-square as a test for statistical significance.

The sensitivity, specificity and predictive values of the EPDS and the PHQ-9 versus the MINI will be analyzed. Factors associated with ante- and post-partum depression and anxiety risk will be analyzed using a logistic regression model.

With regard to the effectiveness of treatment, standard descriptive statistics will be calculated for all questionnaires. Analysis of variance for repeated measurements will be performed to compare the differences between each initial score obtained with the different administered questionnaires and the scores at T1 (end of treatment), T2 (after 6 months) and T3 (after 12 months) will be evaluated. Bonferroni *post hoc* comparisons will be conducted. Treatment effect will be calculated using Cohen’s d for each of the follow-up times. The Reliable Change Index will be calculated for each time, in order to determine any significant clinical changes occurring in each individual case post treatment.

Data will be analyzed using the Statistical Package for Social Science (SPSS) for Windows version 22.0.

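### Objective 5 cannot be answered as worded: temperament is never rated in infants of unaffected mothers, and women enrolled in pregnancy have no pre-treatment score

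*Protocol article*

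**What the plan says.** Main Objectives sets out, as objective 5, to "evaluate the influence of maternal depression and anxiety on the development of baby temperament during a period of a minimum of 12 months" and at most 18 months from birth.

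Three places decide who supplies temperament data:

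- Study Outcomes lists as a secondary outcome "infants’ temperament (only for the infants whose mothers participated in the intervention").
- Phase 3 gives the QUIT, the MINI-Plus and the quality-of-life form selectively: "in the case of clinician-generated diagnosis of perinatal depression and/or anxiety (according to the DSM-5 criteria), these mothers are further assessed". The QUIT is there "to assess the babies’ traits in temperament". This happens before the mother is invited to the intervention.
- Phase 5 repeats the QUIT at the end of the intervention (T1) and at 6 and 12 months (T2, T3). Phase 4 adds one QUIT before the mother–child module.

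On the instrument: "This study uses the QUIT 1–12 and 12–36 month Scales". The section on the QUIT puts its lower age limit at the first month of life.

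For the questionnaires, the Data Analysis Plan uses repeated-measures analysis of variance to "compare the differences between each initial score obtained with the different administered questionnaires and the scores at T1 (end of treatment"), T2 and T3. It introduces this analysis under the effectiveness of treatment.

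**The concern.** An influence of maternal depression and anxiety is a contrast between infants whose mothers are affected and infants whose mothers are not, or at least between degrees of affliction. The plan collects QUIT data on one side of the first contrast and describes no analysis of the second. Follow-up ratings come after treatment, so exposure and treatment cannot be separated.

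The one analysis that would take in QUIT scores is within-person change. Infants change with age in any case, and here the scale also changes at 12 months. If that change were reported under objective 5, development and change of scale could be read as an effect of maternal illness or of therapy. Hypothesis 5 refers to prenatal maternal mental health, so the women enrolled in pregnancy matter most to it. They are the ones without an initial score.

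**Working it through.** **Plan's own sample size.** For a paired t test with d = 0.55, n = 45 and two-sided alpha 0.05 (sidedness is not stated), the noncentral t gives power 0.9503. Allowing for 30% loss, 45 / 0.70 = 64.3, so 65. Both figures in Sample Size reproduce. They are sized for EPDS change, not for objective 5.

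**Contrast.** Under Study Outcomes, exposed infants number up to 65 (about 45 after loss) and unexposed infants 0. Under Phase 3, diagnosed mothers who decline treatment would add one pre-treatment rating each, but they are cases too. Unexposed infants remain 0.

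**Infant age at each visit.** Inputs from the article:

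- entry in pregnancy or with an infant up to 6 months old (Inclusion Criteria);
- evaluation within one week of a positive screen, and the QUIT within the following week (Phases 2 and 3);
- a 10-week intervention (Procedures), with visits at its end and 6 and 12 months later (Phase 5).

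Assumptions: L = 2 to 6 weeks from screening to first session; D = 10 to 16 weeks of intervention (16 if the three partner and three mother–child sessions follow weekly); birth at 40 weeks; 1 month = 4.348 weeks.

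For screening at gestational week g, age at T1 = (g + L + D − 40) / 4.348 months. For an infant aged a months at screening, age at T1 = a + (L + D) / 4.348. T2 and T3 add 6 and 12 months.

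| Screened at | T1 / T2 / T3, months (L + D = 12 weeks) | T1 / T2 / T3, months (L + D = 22 weeks) |
|---|---|---|
| week 12 | −3.7 / 2.3 / 8.3 | −1.4 / 4.6 / 10.6 |
| week 20 | −1.8 / 4.2 / 10.2 | 0.5 / 6.5 / 12.5 |
| week 28 | 0.0 / 6.0 / 12.0 | 2.3 / 8.3 / 14.3 |
| week 36 | 1.8 / 7.8 / 13.8 | 4.1 / 10.1 / 16.1 |
| infant 0 months | 2.8 / 8.8 / 14.8 | 5.1 / 11.1 / 17.1 |
| infant 6 months | 8.8 / 14.8 / 20.8 | 11.1 / 17.1 / 23.1 |

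**Initial score.** The Phase 3 QUIT falls at most two weeks after screening. For a woman screened in pregnancy that is before birth or within the infant's first half month, so below the QUIT's lower age limit. At T1 the infant is at least 1 month old only if g + L + D ≥ 44.35, that is g ≥ 32.4 (12 weeks) or g ≥ 22.4 (22 weeks).

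**Scale.** Every postnatal entrant is at least 14.8 months old at T3, on the 12–36 month scale. Any baseline score, at 6 months or little more, is on the 1–12 month scale. Every baseline-to-T3 comparison in this group therefore crosses scales.

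**Follow-up from birth.** For antenatal entrants, T3 reaches 12 months only if g + L + D ≥ 40: from week 28 (12 weeks) or week 18 (22 weeks). Postnatal entrants pass 18 months at T3 when age at T1 exceeds 6 months. In that case T2 is past 12 months, and it is at most 17.1. Every postnatal entrant therefore has either T2 or T3 between 12 and 18 months.

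**What a within-case analysis could detect.** By Fisher's z, r = tanh[(1.960 + 0.842) / √(n − 3)] at 80% power and two-sided 0.05. For n = 45, tanh(2.802 / 6.481) = 0.41. For n = 65, tanh(2.802 / 7.874) = 0.34. With alpha divided by the six QUIT dimensions, these become 0.49 and 0.42.

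**The case against.** Temperament is a secondary outcome, Hypotheses makes no specific assumption about it, and Strengths and Limitations discloses the lack of a control group. The article is condensed: a model for objective 5 may stand in a fuller plan, and the analysis of variance is offered for treatment effectiveness, not for objective 5. All of this stands, and it lowers the weight of the point. It does not remove it. No analysis plan can supply ratings of infants who are never rated, and the stated limitation does not mention or qualify objective 5.

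The QUIT given before the mother–child module could serve as a first score for an infant born by then. The article does not say whether it does, so it would be wrong to state that the antenatal pairs necessarily drop out.

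Using the scale that fits the infant's age is also not an error. The difficulty is only in attributing change across the two scales.

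A reader might infer that the visits largely miss the 12 to 18 month period. The documents do not support that. Each postnatal entrant has a rating inside it, and so do antenatal entrants screened late enough. Moreover, "during a period of a minimum of 12 months up to a maximum of 18 months from birth" reads more naturally as a length of follow-up than as an age window for measurement.

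**Conclusion.** As worded, objective 5 has no unexposed contrast, and its follow-up ratings are mixed with treatment. This rests on the text alone. That women enrolled in pregnancy lack a pre-treatment rating follows from the QUIT's lower age limit and the Phase 3 timing.

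The limits for follow-up depend on assumed timing: antenatal entrants screened before about week 18 to 28 are followed to less than 12 months from birth, and some postnatal entrants beyond 18. Birth before 40 weeks would make infants older at each visit.

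Two stronger readings are not supported. A reader might infer that temperament data can answer nothing; an association with severity within cases remains possible, though with a restricted range of exposure. A reader might also infer that every rated infant has a treated mother. Study Outcomes implies this, but Phase 3 rates infants before treatment is offered, so the two sections disagree.

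This should be fixed. The primary outcomes are unaffected.

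**What to change.** 1. Restate objective 5 and its conclusion as an exploratory association, within diagnosed or treated pairs, between maternal symptom severity (EPDS and STAI as continuous scores) and each QUIT dimension. Use the scale for the infant's age, with infant age as a covariate.
2. State that T0–T3 change in QUIT scores from the repeated-measures analysis will not be read as an effect of maternal depression or of treatment.
3. State the infant ages that the visits deliver, and whether the QUIT before the mother–child module counts as a first score.
4. Reconcile Phase 3 and Study Outcomes on who contributes QUIT data.

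This needs rewording and no new data. The cost is a narrower claim that can detect only fairly large correlations (about 0.41 at n = 45). Keeping the objective as worded would require QUIT ratings from mothers who screen negative. Even then, follow-up comparisons would set treated cases against untreated non-cases.

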### Measures

#### Edinburgh Postnatal Depression Scale

The EPDS (Cox et al., 1987) is the most widely used screening tool for depressive symptoms during the perinatal period (de Moraes et al., 2017; Ukatu et al., 2018). It is a self-rating scale containing 10 items about symptoms of depression such as anhedonia, feelings of guilt, lethargy, sleep disturbance and suicidal ideation. The answer to each item is on a four-point Likert scale with which mothers indicate the frequency with which they have experienced the corresponding symptom during the past 7 days. The total score ranges from 0 to 30, with higher scores indicating more severe depressive symptoms. The internal consistency of the Italian version of the EPDS (Cronbach standardized alpha) was 0.80 (Benvenuti et al., 1999), which is similar to the value reported by Cox in the first validation study (0.87). The sensitivity, specificity, and positive predictive value of the Italian version were recorded as 55.6, 98.9, and 90.9%, respectively, based on a cut-off score ≥12, making it a reliable and valid screening tool for perinatal depression. Furthermore, a recent study (Smith-Nielsen et al., 2018) found that a score of 11 or more is the optimal cut-off for depression according to both DSM-5 (American Psychiatric Association, 2013) and ICD-10 criteria (World Health Organization, 1992).

#### Patient Health Questionnaire-9

The PHQ-9 (Kroenke et al., 2001) is the first choice for depressive symptoms in non-psychiatric primary care settings (Thase, 2016) and the third most common screening tool for postpartum depression (de Moraes et al., 2017). It is a self-rating scale containing nine items about symptoms of depression such as anhedonia and low mood, in conjunction with problems concerning physical activity, appetite, concentration, energy, self-esteem, sleep and suicidal ideation. The answer to each item is on a four-point Likert scale with which mothers indicate the frequency with which they have experienced the corresponding symptom during the past 14 days. The total score ranges from 0 to 27, with higher scores indicating more severe depressive symptoms. During the perinatal period, a score of ≥10 is usually recommended to define the presence of depression (Flynn et al., 2011; Sidebottom et al., 2012; Marcos-Nájera et al., 2018). Furthermore, two of these studies evaluated the factor structure of the PHQ-9, finding that a three-factor (cognitive-affective, somatic, pregnancy-related) model is adequate during pregnancy (Marcos-Nájera et al., 2018). The internal reliability (Cronbach alpha) of the PHQ−9 was 0.86 in an obstetrics−gynecology sample (Kroenke et al., 2001). The sensitivity, specificity, and positive predictive value of the PHQ-9 Italian version (Mazzotti et al., 2003) were recorded as 39, 29, and 93%, respectively, for any depressive syndrome. Furthermore, the PHQ-9 can be used to assess depression severity based on the DSM-5 (American Psychiatric Association, 2013) diagnostic criteria (Spitzer et al., 2014).

